### Measures

Our primary outcomes are the modified Roland Scale [8] (a measure of back pain-related physical disability) and a 0–10 numerical rating scale of pain intensity (0 = no pain, 10 = pain as bad as could be) [9]. A 2 or 3-point difference on the Roland Scale is the smallest clinically important difference found in studies of patients with other types of back pain [8,10].

Subjects are asked about their use of medications (anti-osteoporosis, analgesic, and steroid) to assess for potential confounding in the outcomes analyses. We will also collect a self-report version of the Charlson comorbidity index [11]. Secondary outcome measures include the modified Deyo-Patrick Pain Frequency and Bothersomeness Scale [12], the SF-36 version 2 (a general health-related quality of life measure) [13], the Strength of Function (SOF) and Activities of Daily Living (ADL), the EQ-5D (a measure of health state preferences) [14], and the Osteoporosis Assessment Questionnaire (OPAQ) body image domain (an osteoporosis-specific functional status instrument) [15].

A back pain resource use questionnaire is used to assess the medical care costs associated with vertebroplasty. Subjects are asked to provide information concerning outpatient and office visits, including the medical specialty of the provider; the number of visits; the tests, treatments, or devices received at the visit; and the average length of time for each visit. Hospitalizations and ambulatory surgery are also recorded in the questionnaire. Finally, we will assess the name, dose, and frequency of use of osteoporosis medications, analgesics, and any other drugs potentially used for back pain.

Adverse events and serious adverse events will be collected at each time point (clinic visit and telephone call). Data acquired at the visits and telephone calls is entered into the electronic database. Any medical problems are "caught" in the electronic system and an automatic e-mail goes to the study principal investigator and the database controller. This facilitates quick action on any serious adverse event. The DSMB and NIAMS are notified of adverse events using KAI, Research Inc. as the intermediary for notification.

Follow up radiographs will be completed for all subjects at the 12 month clinical visit. The study will pay for these x-rays. Adjacent fractures, if there are any, will be able to be seen on these radiographs.

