For primary analyses, an "intention-to-treat" strategy will be employed, such that each subject is analyzed in the group to which he or she is randomized, regardless of actual compliance with the intended intervention. This strategy requires minimal assumptions and maintains the random allocation, although intervention effects may be "diluted" if cross over between procedures is high. We will stratify all analyses for site. Non-adherence and/or dropout complicate analysis of follow-up data. Consideration of missing data is essential to characterize the potential for selection bias through attrition. When appropriate, missing follow-up data for subjects who withdraw will be imputed.

The primary outcomes of Roland and pain measure will be assessed at the one-month time point. This allows adequate time for any intervention benefit to manifest, and is the final assessment prior to the opportunity to select further treatment (crossover). The primary analysis will test for the efficacy of vertebroplasty using a permutation test based on the randomization distribution. Such analysis allows formal inference relying solely on the random assignment of subjects for validity (i.e., makes no additional statistical assumptions). Confidence intervals for the magnitude of treatment effect will be obtained using linear regression with a treatment indicator as the predictor of interest and using dummy variables to stratify on site. We will perform a similar analysis using the 0–10 numerical pain rating scale at one month. Secondary analyses will describe the complete time profile for the Roland and the pain ratings through one year using methods appropriate for the analysis of repeated measures [16].

In addition to hypothesis tests based on the randomization scheme, we will conduct secondary analyses that adjust for important baseline characteristics, such as baseline pain severity, and functional status. We will conduct limited exploratory analyses to assess evidence for differential treatment response by subject subgroups by testing treatment-covariate interactions for factors that are specified *a priori *in a detailed analysis plan to be created prior to data analysis. We will also perform a subgroup analysis examining whether enrolling early or late in the study had an effect on outcome. This will help determine if a significant learning curve was present and, if so, the magnitude of the effect.

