The serious adverse event (SAE) complication rates occurring within one month of surgery for the device-treated and control subjects will be evaluated descriptively in aggregate and separately. The SAE rate for each group will be estimated and the corresponding 95% exact binomial confidence intervals will be computed. If the number of events is sufficiently large to allow more sophisticated analysis, the rates between the vertebroplasty and control subjects will be compared by logistic regression with covariate adjustment. The data will be presented by total numbers of events and by total numbers of subjects with at least one event. The complication rates including subsequent fractures will be descriptively analyzed through two years post-treatment. The rates and the corresponding 95% exact confidence intervals will be computed.

Based on 12-month plain radiographs, as compared to baseline radiographs, we will compare the proportion of subjects in the two study arms suffering at least one new-onset fracture using the binomial test. We will use the Student t-test to compare the two groups in terms of the mean number of new fractures and the mean number of vertebral levels between the treated levels and new fracture levels.

Non-serious adverse events will be tabulated individually and overall through one year post treatment. The rates will be estimated for the device-treated and control subjects separately and the exact binomial 95% confidence limits will be calculated.

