### Sample Size

In unpublished pilot data on 88 patients, we found an 8.6 point average reduction on the Roland (standard deviation of 6.7) at 4 weeks following the vertebroplasty procedure. We originally planned to enroll 249 subjects but had to adjust our expectations to 166 subjects due to difficulty with enrolment. With at least 90% follow-up at one month, we expect to have 75 subjects in each arm (150 total) assessed. This sample size yields 95% power to detect a 4-point effect size, and maintains good power for a 3-point effect size (78% power).

We will use a 0–10 numerical pain rating scale to test the hypothesis that short and long-term pain relief is greater in the percutaneous vertebroplasty group than in the control group. In a pilot study, we found a mean reduction of 7.1 (2.7 SD) points on this pain rating scale in a group of patients who received vertebroplasty [24]. A sample size of 150 has greater than 95% power to detect an effect size of 1.75 and a greater than 80% power to detect a 1.25-point effect size.

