### Data Management

Data acquisition, handling, and storage are under the direction of the senior programmer of the Data Coordinating Center at the University of Washington. An HTML form-based web application is in use for conducting subject assessments as an efficient method for managing data for this multi-center, national trial. Data will be housed in a secure, centralized database at the University of Washington. The system will automatically perform edit and logic checks to validate the data for quality and completeness as they are being entered. A quality control audit will be performed on a monthly basis and the results printed in an interim report. Staff at the data-coordinating center will monitor the compliance of each study hospital with the study procedures and data quality.

We will document the number and proportion of subjects eligible for and compliant with each follow-up. Careful efforts will be made to minimize missing data, though some will inevitably occur. Subjects who withdraw from the study will be tabulated with the reasons for the withdrawal. Subjects who die during the study (unrelated to study or procedure) will be tabulated also. If the proportion of subjects withdrawn is larger than the expected 15% at one month and additional 10% at one year from either arm, an analysis of the demographic and prognostic characteristics will be made between subjects who withdraw and those who remain in the study. For continuous variables, parametric or non-parametric analysis of variance will be used. For categorical variables, Chi-square or Fisher's exact test will be applied.

When individual items are missing from a scale, we will calculate the percent of missing items. If the missing items are less than 10%, we will impute values using the mean of the remaining items. If more than 10%, the scale score will be missing, and unavailable for analysis at that time point.

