## Discussion

Although extensively utilized throughout North America for palliation of pain, vertebroplasty still has not undergone rigorous study. The study outlined above represents the first randomized, controlled study that can account for a placebo effect in the setting of vertebroplasty.

Waning enrolment caused the addition of foreign sites to the study to have the number of subjects needed for an acceptable sample. Approval was obtained from the State Department and the NIH and some foreign sites were initiated into the study and enrolment increased. We now anticipate enrolling a total of 100 subjects. Assuming a 90% follow up rate at one month, we maintain good power (80%) to detect group differences in Roland of 4.0 or more and 87% power for differences in pain of at least 1.75.

Results from this study should provide compelling evidence as to whether or not internal stabilization of non-healing, painful, osteoporotic vertebral compression fractures offers clinical benefit.

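### One-year non-serious adverse-event rates are planned as exact binomial proportions although up to 25% withdrawal is expected; over all treated subjects this understates the rates by roughly 6–19%

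*Protocol article*

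**What the plan says.** The Analysis section sets the window and the estimator for non-serious events: "Non-serious adverse events will be tabulated individually and overall through one year post treatment", followed by "The rates will be estimated for the device-treated and control subjects separately and the exact binomial 95% confidence limits will be calculated". It names the two groups but not who enters the denominator or how a subject who leaves early is counted.

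The Measures section describes ascertainment: "Adverse events and serious adverse events will be collected at each time point (clinic visit and telephone call".

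Two sections give different losses at one month. Data Management plans an analysis of withdrawals if they are "larger than the expected 15% at one month and additional 10% at one year from either arm". Sample Size says: "With at least 90% follow-up at one month, we expect to have 75 subjects in each arm (150 total) assessed". The Discussion lowers the target ("We now anticipate enrolling a total of 100 subjects") and keeps the 90% follow-up assumption.

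The only general provision for missing follow-up is "When appropriate, missing follow-up data for subjects who withdraw will be imputed". It is not tied to adverse events.

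**The concern.** A binomial proportion estimates a one-year risk only if every subject in the denominator is observed for the whole year. The plan itself expects up to a quarter not to be. With all treated subjects in the denominator, a subject who leaves at month 1 counts as event-free for eleven months in which routine contacts could record nothing, so the rate is pulled down. With completers only, that bias disappears if withdrawal is unrelated to events, but recorded events in subjects who later left are thrown away, and the estimate is biased if events prompt withdrawal.

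At stake is the reported frequency of non-serious harms in each group. The error runs towards making both procedures look safer than they are, and an interval labelled exact would suggest more certainty than the data carry.

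**Working it through.** **The plan's own figures.** The article gives no adverse-event rate or interval to reproduce. Its follow-up and power figures do reproduce: 166 × 0.90 = 149.4, about 150, or 75 per arm; with SD 6.7 and two-sided alpha 0.05 (assumed, not stated), power is 95.5% for 4 Roland points and 78.3% for 3, against the stated 95% and 78%. So the power statement rests on 10% loss at one month. At the 15% of Data Management the number would be 166 × 0.85 = 141.

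**Inputs from the article.** One-month loss 15% or 10%; a further 10% by one year; about 50 per arm (100 enrolled) or 83 per arm (166 enrolled).

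**Assumptions, because the article gives no value.** All treated subjects form the denominator; withdrawal is unrelated to events and spread evenly within each interval; nothing is recorded after withdrawal; event risk and timing are varied.

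**Bias.** Let f be the share of first events that fall in month 1, and let m1 and m2 be the mean proportions still followed in month 1 and in months 1–12. Then

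reported rate / true risk = f × m1 + (1 − f) × m2.

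- 15% loss: m1 = (1.00 + 0.85)/2 = 0.925; m2 = (0.85 + 0.75)/2 = 0.80.
- 10% loss: m1 = (1.00 + 0.90)/2 = 0.95; m2 = (0.90 + 0.80)/2 = 0.85.

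| Share of events in month 1 | Ratio, 15% loss | Ratio, 10% loss |
|---|---|---|
| 1/12 (even timing) | 0.810 (19% too low) | 0.858 (14%) |
| 1/2 | 0.863 (14%) | 0.900 (10%) |
| 3/4 | 0.894 (11%) | 0.925 (7.5%) |
| 9/10 | 0.913 (9%) | 0.940 (6%) |

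Example: with 15% loss and even timing, a true 30% is reported as 0.30 × 0.81 = 24.3%.

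**Sensitivity to withdrawal timing** (15% loss, even event timing). If everyone who leaves does so at the end of an interval, the ratio is 1/12 + 0.85 × 11/12 = 0.86. If all leave at its start, it is 0.85/12 + 0.75 × 11/12 = 0.76. Reading the additional 10% as a share of those remaining (23.5% in total) gives about 0.82.

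**Coverage of the exact 95% limits for the true one-year risk.** Event counts were taken as binomial with probability ratio × true risk, and coverage was found by enumerating all counts, at 15% loss:

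| True risk | 50 per arm, even | 83 per arm, even | 50 per arm, half in month 1 | 83 per arm, half in month 1 |
|---|---|---|---|---|
| 5% | 99.6% | 96.1% | 99.5% | 96.5% |
| 10% | 97.9% | 96.6% | 98.0% | 97.3% |
| 20% | 92.3% | 88.3% | 94.4% | 92.2% |
| 30% | 88.8% | 82.6% | 92.7% | 89.4% |

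At 50 per arm, 30% risk and even timing, 11.1% of intervals lie wholly below the truth; without withdrawal it is 1.8%. Coverage without withdrawal is about 95–99% throughout. With 10% loss and even timing, coverage of a 30% risk is 92.5% at 50 per arm and 89.0% at 83. With 10% loss and nine tenths of events in month 1 it is 96.0% and 94.9%, so little under-coverage is left.

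**The case against.** The strongest reply is that the denominator is not in the article. A condensed article may leave the safety population to the full plan, and completers only would be unbiased under the very assumption used above. This stands in part: the size of the bias is conditional on an all-treated denominator. But the article does fix the estimator and the window, and neither denominator is satisfactory when up to a quarter of subjects are expected to leave.

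Several stronger readings are tempting and are not supported.

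- *That adverse-event rates in general are biased by a fixed amount.* The quoted sentences cover non-serious events only. Serious events within one month are a separate analysis. No event risk or timing is documented, so no single percentage follows.
- *That the limits miss the truth throughout.* Exact limits are conservative for rare events. For risks of 2–10% with even timing and 15% loss, mean coverage is 97–98.5% at 50 to 83 per arm, with isolated dips to about 93–95%.
- *That the comparison of harms between arms is biased.* No test between arms is planned for these events, and nothing in the article indicates that withdrawal will differ by arm.
- *That nothing can be known after withdrawal.* The Procedures section asks subjects to report problems to the physician, and Safety Monitoring covers changes in health at any time. Some later events may surface, which would shrink the bias.

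It is also fair that crude incidence with exact limits is a common safety summary, that log-log limits are undefined when a row has no events, and that crossover from one month onward mixes exposures in one-year rates. A cumulative-incidence estimate does not cure the last of these.

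**Conclusion.** The concern holds in a limited form. Over all treated subjects, with withdrawal unrelated to events and spread evenly within each interval, one-year non-serious event rates are understated by roughly 6–19%: 9–19% at 15% one-month loss and 6–14% at 10%. If all withdrawals came at the start of each interval, it could reach 24%. The direction was downward in every all-treated scenario examined.

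Under-coverage matters for true risks of about 20% or more, which makes the overall rate the row most exposed, since it is at least as high as any single event's. It shrinks when most events cluster around the procedure. Rows for single events at 5–10% are essentially unaffected.

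These are descriptive tables; no primary result depends on them. The change is worth making because the plan's own attrition figures foresee the problem and the remedy is inexpensive.

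**What to change.** In the Analysis section, for the overall rate and the common non-serious events through one year:

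- Report the 12-month cumulative incidence of a first event per group, with death as a competing event (Aalen-Johansen), censoring at the last completed contact. The article does not say that onset dates are recorded; if they are not, assign the event to the interval between contacts.
- Add events per observed person-time.
- Keep raw counts of events and subjects in every row, and keep exact binomial limits for rare and zero-event rows, with the denominator stated.

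Separately, reconcile the one-month loss of 15% in Data Management with the 10% implied in Sample Size and the Discussion.

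The cost is a change of wording and a modest amount of extra analysis. Intervals for the common events become slightly wider and are no longer exact, and the estimate relies on withdrawal being uninformative, which should be said beside the table.

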### Safety Monitoring

If at any time after the procedure (vertebroplasty or control) is performed there are any changes in physical health, the event(s) will be reported to the appropriate authorities (DSMB, NIH, and all site PIs and IRBs) as soon as it is known and will be followed until resolution.

An external six-member Data Safety Monitoring Board (DSMB) is monitoring the study in accordance with NIAMS guidelines. The DSMB determined appropriate stopping criteria and will review the data after 73 and 90 subjects have one-month Roland and pain outcomes for evidence of treatment efficacy or unusual rates of adverse outcomes. KIA Research, Inc. manages the safety monitoring for NIAMS, and serious adverse events will be reported directly to NIAMS and KIA Research, Inc., who will distribute this information to the DSMB chair and safety officer, as they occur. Subsequent vertebral fractures (adjacent and non-adjacent) will be a reportable event, not an adverse event. The principal investigator will notify each site IRB of any death regardless of where the death occurred.

### Sample Size

In unpublished pilot data on 88 patients, we found an 8.6 point average reduction on the Roland (standard deviation of 6.7) at 4 weeks following the vertebroplasty procedure. We originally planned to enroll 249 subjects but had to adjust our expectations to 166 subjects due to difficulty with enrolment. With at least 90% follow-up at one month, we expect to have 75 subjects in each arm (150 total) assessed. This sample size yields 95% power to detect a 4-point effect size, and maintains good power for a 3-point effect size (78% power).

We will use a 0–10 numerical pain rating scale to test the hypothesis that short and long-term pain relief is greater in the percutaneous vertebroplasty group than in the control group. In a pilot study, we found a mean reduction of 7.1 (2.7 SD) points on this pain rating scale in a group of patients who received vertebroplasty [24]. A sample size of 150 has greater than 95% power to detect an effect size of 1.75 and a greater than 80% power to detect a 1.25-point effect size.

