**Methods/Designs:**

Our goal is to test the hypothesis that patients with painful osteoporotic vertebral compression fractures who undergo vertebroplasty have less disability and pain at 1 month than patients who undergo a control intervention. The control intervention is placement of local anesthesia near the fracture, without placement of cement. One hundred sixty-six patients with painful osteoporotic vertebral compression fractures will be recruited over 5 years from US and foreign sites performing the vertebroplasty procedure. We will exclude patients with malignant tumor deposit (multiple myeloma), tumor mass or tumor extension into the epidural space at the level of the fracture.

We will randomly assign participants to receive either vertebroplasty or the control intervention.

Subjects will complete a battery of validated, standardized measures of pain, functional disability, and health related quality of life at baseline and at post-randomization time points (days 1, 2, 3, and 14, and months 1, 3, 6, and 12). Both subjects and research interviewers performing the follow-up assessments will be blinded to the randomization assignment. Subjects will have a clinic visit at months 1 and 12. Spine X-rays will be obtained at the end of the study (month 12) to determine subsequent fracture rates. Our co-primary outcomes are the modified Roland score and pain numerical rating scale at 1 month.

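### The Abstract and Sample Size section still plan 166 subjects, but the Discussion anticipates 100, at which the stated 78% (3 Roland points) and >80% (1.25 pain points) powers become about 56% and 58–59%

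*Protocol article*

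**What the plan says.** All quotes are from the protocol article.

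- **Abstract, Methods/Designs:** "One hundred sixty-six patients with painful osteoporotic vertebral compression fractures will be recruited over 5 years".
- **Sample Size:** 166 is itself a revision: "We originally planned to enroll 249 subjects but had to adjust our expectations to 166 subjects due to difficulty with enrolment". The evaluable number follows: "With at least 90% follow-up at one month, we expect to have 75 subjects in each arm (150 total) assessed". For the Roland, the section gives 95% power for 4 points and says the sample "maintains good power for a 3-point effect size (78% power"). For pain, it gives more than 95% for 1.75 points and "greater than 80% power to detect a 1.25-point effect size".
- **Discussion:** "We now anticipate enrolling a total of 100 subjects". With 90% followed up at one month, it gives 80% power for 4.0 Roland points and 87% for 1.75 pain points. It gives no power for 3 Roland points or 1.25 pain points.
- **Measures:** "A 2 or 3-point difference on the Roland Scale is the smallest clinically important difference", a figure the same sentence attributes to studies of other types of back pain.
- **Safety Monitoring:** the DSMB reviews the data once 73 and once 90 subjects have one-month Roland and pain outcomes.

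**The concern.** The Sample Size section was updated for the cut from 249 to 166, but neither it nor the Abstract was updated for the later cut to 100. A reader of either place takes away a trial two-thirds larger than the one expected (166/100 = 1.66).

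The Sample Size section reports power for two effects per outcome. The Discussion carries only the larger of each pair to the new target, and nowhere does the article say that the 78% and >80% figures have lapsed. These concern the co-primary outcomes, and 3 Roland points is the upper end of the smallest important difference that the article cites. What is at stake is whether the stated sensitivity to the smaller effects is one the trial can still deliver.

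**Working it through.** **Inputs**

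- SD: Roland 6.7, pain 2.7 (Sample Size).
- Assessed per arm: 75 under the 166 plan (Sample Size); 100 × 0.90 / 2 = 45 under the 100 plan (Discussion).
- Significance level: not stated in the article. Two-sided 0.05 is assumed because it reproduces all six stated powers. One-sided 0.05 does not (it gives 86% for 3 Roland points at 75 per arm), nor does two-sided 0.025 (69%).

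**Method.** For a difference Δ with n per arm, SE = SD × √(2/n), and power ≈ Φ(Δ/SE − 1.96). The two-sample t-test power (noncentral t) is given beside it.

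**Step 1: reproduce the Sample Size figures, n = 75 per arm.** SE = 6.7 × √(2/75) = 1.094 for the Roland and 2.7 × √(2/75) = 0.441 for pain.

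| Effect | Δ/SE | Normal | t-test | Stated |
|---|---|---|---|---|
| Roland 4 | 3.656 | 95.5% | 95.3% | 95% |
| Roland 3 | 2.742 | 78.3% | 77.8% | 78% |
| Pain 1.75 | 3.969 | 97.8% | 97.6% | >95% |
| Pain 1.25 | 2.835 | 80.9% | 80.4% | >80% |

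**Step 2: reproduce the Discussion figures and add the two it omits, n = 45 per arm.** SE = 6.7 × √(2/45) = 1.412 and 2.7 × √(2/45) = 0.569.

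| Effect | Δ/SE | Normal | t-test | Stated |
|---|---|---|---|---|
| Roland 4 | 2.832 | 80.8% | 80.0% | 80% |
| Pain 1.75 | 3.074 | 86.8% | 86.0% | 87% |
| Roland 3 | 2.124 | 56.5% | 55.6% | none |
| Pain 1.25 | 2.196 | 59.3% | 58.4% | none |

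The model that returns every printed power also returns the two missing ones: about 56% and 58–59%.

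**Step 3: vary follow-up at 100 enrolled.** If all 100 were assessed (50 per arm), power would be 60–61% for 3 Roland points and 63–64% for 1.25 pain points. With the 15% one-month withdrawal that Data Management calls expected (42.5 per arm on average), it would be 53–54% and 56–57%. No follow-up rate at 100 enrolled restores 78% or 80%.

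**Step 4: the DSMB looks.** Against 150 assessed, looks at 73 and 90 fall at 73/150 = 49% and 90/150 = 60% of the information. Against 90 assessed, they fall at 73/90 = 81% and 90/90 = 100%, so the second look is the whole expected evaluable sample.

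**The case against.** **No calculation is wrong.** This stands: every printed power is correct for the sample size printed with it. The defect is an outdated target in two places, not an arithmetic error.

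**The cut to 100 is disclosed.** This stands in part. The Discussion marks 100 as the latest figure and gives new powers for it, so a reader of the whole article can tell which number is current. A reader of the Abstract or the Sample Size section cannot. The Discussion makes no false claim about the smaller effects, but it does not withdraw the earlier ones.

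**The 2 to 3-point difference is not this trial's own margin.** This stands. It comes from other types of back pain, and the article gives no important difference for pain at all. One may not say that the article declares 3 Roland points or 1.25 pain points clinically important for these patients. The point rests on the fact that the article chose these effects to report power for.

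**A stronger reading is tempting.** A reader might infer that, at 100 subjects, a null result could not exclude a worthwhile benefit, against the Discussion's statement "Results from this study should provide compelling evidence as to whether or not" there is benefit. The expected 95% half-width for the Roland at 45 per arm is 1.987 × 1.412 = 2.81, so an observed difference of zero leaves 2 points inside the interval. But at 75 per arm the half-width is 1.976 × 1.094 = 2.16, and 2 points is inside there too. The article never claimed power for 2 points. That argument therefore does not follow from the discrepancy. The article already plans confidence intervals, and how a null result will be read may be left to an analysis plan that is not shown.

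**The stated 87% for pain needs no correction.** This stands: 86.8% is the normal approximation and 86.0% the t-test value. Either is acceptable.

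**Conclusion.** The concern holds as a consistency fault with a measurable consequence. Two enrolment targets stand in the current text, and the powers attached to the larger one do not carry over to the smaller. At 90 assessed, power for 3 Roland points is about 56% rather than 78%, and for 1.25 pain points 58–59% rather than just over 80%: a loss of about 22 percentage points each. The powers the Discussion states for 4.0 and 1.75 points are sound.

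This rests on the article's SDs, equal allocation, 90% follow-up and an assumed two-sided 5% level. It does not show a miscalculation or concealment of the reduced target, and it is no ground for calling the trial's design invalid.

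**What to change.** 1. State one current enrolment target, 100, in the Abstract and the Sample Size section. The steps from 249 to 166 to 100 can stay as history.
2. In the Sample Size section, replace the 166-based powers with those at 90 assessed: Roland 4 points 80%, 3 points about 56%; pain 1.75 points 86–87%, 1.25 points about 58–59%. State the significance level and the SDs beside them.
3. Keep the qualifier on the 2 to 3-point Roland difference wherever the 3-point power is set against it.
4. Reconcile the DSMB looks at 73 and 90 subjects with the chosen target, and say whether the look at 90 is still an interim one.

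The changes to the sample size are text only: no extra patients and no change to the outcomes or the primary analysis. The cost is a less favourable stated power for the smaller effects.
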